## Abstract

**Background:**

General practitioners (GPs) and patients find it difficult to talk about risk of future disease, especially when patients have asymptomatic conditions, and treatment options are unlikely to cause immediate perceptible improvements in well-being. Further studies in risk communication training are needed. Aim:1) to systematically develop, describe and evaluate a complex intervention comprising a training programme for GPs in risk communication and shared decision-making, 2) to evaluate the effect of the training programme on real-life consultations between GPs and patients with high cholesterol levels, and 3) to evaluate patients' reactions during and after the consultations.

**Methods/Design:**

The effect of the complex intervention, based around a training programme, will be evaluated in a cluster-randomised controlled trial with an intervention group and an active control group with 40 GPs and 280 patients in each group.

The GPs will receive a questionnaire at baseline and after 6 months about attitudes towards risk communication and cholesterol-reducing medication. After each consultation with a participating high cholesterol-patient, the GPs will complete a questionnaire about decision satisfaction (Provider Decision Process Assessment Instrument). The patients will receive a questionnaire at baseline and after 3 and 6 months. It includes questions about adherence to chosen treatment (Morisky Compliance Scale), self-rated health (SF-12), enablement (Patient Enablement Instrument), and risk communication and decision-making effectiveness (COMRADE Scale). Prescriptions, contacts to the health services, and cholesterol level will be drawn from the registers.

In each group, 12 consultations will be observed and tape-recorded. The patients from these 24 consultations will be interviewed immediately after the consultation and re-interviewed after 6 months.

Eight purposefully selected GPs from the intervention group will be interviewed in a focus group 6 months after participation in the training programme.

The process and context of the RISAP-study will be investigated in detail using an action research approach, in order to analyse adaptation of the intervention model to the specific context.

**Discussion:**

This study aims at providing GPs and patients with a firm basis for active deliberation about preventive treatment options, with a view to optimising adherence to chosen treatment.

**Trial registration:**

ClinicalTrials.gov Protocol Registration System NCT01187056

## Background

Much attention has been given to how risk information should be communicated to patients with established conditions requiring treatment or specific surveillance strategies [1-3]. In prevention of disease, however, risk communication needs further elaboration; especially where preventive treatments are not likely to cause immediate perceptible improvements in well-being. This is a particular problem in the prevention of cardiovascular disease which is a major cause of morbidity, impaired quality of life and premature death worldwide. It has been argued that preventive treatment to lower the risk of cardiovascular disease is underused as a result of both general practitioners' low adherence to clinical guidelines and patients' low adherence to preventive treatment [4-6]. The issue therefore arises as to whether prevention of cardiovascular disease can be improved through enhanced communication.

High cholesterol is a well-defined risk factor for cardiovascular disease [7,8]. It is asymptomatic and usually detected by opportunistic screening in primary care. A change of life style is usually recommended to patients with high cholesterol. When this does not achieve sufficient reduction in the cholesterol level, cholesterol-reducing medication is usually suggested. Cholesterol-reducing medication has been shown to effectively reduce the risk of fatal heart disease [9]. The risk reduction depends on continuous (lifelong) medication. However, a review on prevention of cardiovascular disease has shown that 50% of all patients prescribed with cholesterol-reducing medication stop treatment within 6 months, with a further decline after one year. This decline is most prominent in patients with no symptoms of cardiovascular disease [10,11]. When patients do not comply with prescribed preventive medication for cardiovascular disease, the benefits will not be fully achieved [12,13].

Non-adherence to preventive medication may be due *inter alia *to inadequate knowledge about risk of disease, uncertainty about treatment benefits, and anxiety about side-effects [14]. In order for patient-centred care to be effective, it is important to support initiatives that ensure sufficient information about risks and benefits [15,16].

The choice to prioritise preventive treatment over watchful waiting should be taken collectively by the general practitioner (GP) and the individual patient [17]. Such co-operation is often complicated by contradictory perceptions of risk of disease and dangers associated with preventive treatment [18]. This is consistent with sociological and ethnographic studies showing that perceptions and deliberations of risk and danger are context-specific and embedded in knowledge traditions and complex socio-cultural relationships [19,20].

Shared decision-making (SDM) has been developed to enhance patient autonomy and engage patients in the process and responsibility of decision-making [21]. It includes a key component of risk communication [22]. SDM enhances patient involvement, though its benefits on patient-based outcomes, such as knowledge, anxiety, satisfaction and actual choice or adherence to chosen treatments (including choosing no treatment if relevant) are less clear [23,24]. SDM can be supported in different ways. Firstly, patient decision aids have been developed to facilitate patient-doctor communication about risk. Patient decision aids assist patients in making informed value-based choices by providing evidence-based information about a health condition, treatment options (including no-treatment), and potential benefits and harms, including risk numbers in different formats [25]. Secondly, training of healthcare professionals in shared decision-making, risk communication, and use of patient decision aids has been undertaken. Some studies have shown positive results in terms of patient satisfaction, patients' knowledge about risk, healthcare professional/patient-relationship, and patients' involvement in the medical decision [26,27] but this has been inconsistent in the literature to date [2].

There are a number of gaps in the evidence base. Training methods and training extent are often poorly described in published articles [28-30]. Few studies have determined effects of risk communication and/or decision aids on adherence to the chosen therapy [2]. Furthermore, only a few observational studies of doctor/patient risk communication have investigated real-life consultations [31-36]. Further studies in these areas of risk communication for disease prevention are needed as are studies about risk communication training for GPs and the use of decision aids. These studies need to develop and evaluate interventions that address a range of likely difficulties - in training and adoption of SDM and risk communication skills, use of decision aids with real patients, and follow-up of their effectiveness as patients try to adapt treatment plans to their everyday lives. By nature these are 'complex interventions' [37] and will benefit from multi-faceted evaluation [38].

## Objective

The objective of the RISAP study is 1) to systematically develop, describe and evaluate a complex intervention comprising a training programme for GPs in risk communication and shared decision-making, 2) to evaluate the effect of the training programme on real-life consultations between GPs and patients with high cholesterol, and 3) to evaluate the patients' reactions during and after the consultations and adherence to chosen treatment plans.

RISAP is an acronym for **Ris**k Communication in Gener**a**l **P**ractice.

The hypotheses are that the intervention group patients will have higher adherence to chosen treatment, have better self-rated health and fewer contacts with health services, have better satisfaction with treatment decision, and experience no increased anxiety, compared to the control group patients.

## Methods and design

### Participants

GPs in Region Central and Region North, Denmark, are invited to the study.

Patients are at least 18 years old, and have high cholesterol corresponding to a recommendation for cholesterol-reducing medication according to Danish clinical guideline for general practice [39]. The patients are recruited after their high cholesterol has been detected and when treatment options are to be discussed.

Patients with CVD or DM are excluded from the study, as are patients already receiving cholesterol-reducing medication and patients unable to speak and read Danish.

### Intervention

The intervention is a training programme for GPs in risk communication and shared decision-making. It consists of workshop sessions of 2×2 hours' duration and includes teacher-led discussions and GP role plays relating to risk communication, shared decision-making principles, and primary prevention of cardiovascular disease in general practice. In addition, the GPs will have training in the use of visual representations of risk and risk reduction, as well as a patient decision aid developed specifically for the training programme (please see "Development of the intervention" below).

The control group GPs will receive 2 hours of training in the primary care guideline for prevention of cardiovascular disease [39].

In both intervention group and control group, each workshop session will have 6-10 GPs led by two teachers from the teaching group (JT/BH/TL). The control group GPs will be invited to receive the full training programme after the conclusion of the study.

After participation in the workshop sessions, the GPs will return to their practices. When the GP identifies a patient with high cholesterol and is likely to suggest preventive pharmacological treatment, the GP will invite the patient to participate in the study. If the patient accepts participation, the GP will use the skills from the sessions (either intervention or control) during the consultation. Each GP will invite and recruit a minimum of 7 (consecutive) patients. Recruitment will be reimbursed with a fee of 300 DKK (35 £/40 €) per patient.

The study will be administered by three researchers and members of the RISAP project group. It will, however, also be administered by the participating GPs as they invite patients to the study.

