### Study Design and Randomisation

The effect of the complex intervention, based around a training programme for GPs, will be evaluated in a cluster-randomised controlled trial with an intervention group and an active control group [37,40,41].

Each participating practice will form a 'cluster'. Practices will be randomised to participate in either intervention or control group. The randomisation of the GPs is stratified according to single-handed practice or group practice, gender (male/female/both sexes) and age (average age of participating GPs if more than one GP from a group practice participate), and urban or rural practice. Randomisation will be undertaken by random number generation, and allocations by a program made by an independent statistician will be concealed from those implementing the intervention. Both GPs and patients will be informed that the study investigates cardiovascular risk management but the patients will be 'blinded' to which group they are in.

In each group, 12 consultations will be observed and tape-recorded by a researcher (PK). The consultations will be divided between 4 GPs, each with 3 patients. The GPs will be selected according to gender and age (1 male + 1 female GP ≥ 48 years, 1 male GP + 1 female GP < 48 years). The patients from these 2×12 consultations will be interviewed immediately after the consultation and re-interviewed after 6 months. The interview will be of approx. 45 minutes duration. The tape-recorded consultation will be played back during the interview with the patient, using the Think Aloud-method [42,43]. The observations during the consultation will be written down as ethnographic field notes [44]. The aim is to make a rich and detailed 'thick' description [45] of the consultation. The patient interviews after the consultations will focus on the patients' immediate reactions to risk communication and decision-making in the consultation, using a semi-structured interview guide with open questions and play back of the tape-recorded consultation. The patients will be re-interviewed after 6 months.

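### Invitation depends on the trained GP's own intention to suggest a drug, so the arms may recruit different patients after randomisation

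*Protocol article*

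**What the plan says.** All references are to the protocol article.

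- **Allocation** (Study Design and Randomisation): "Practices will be randomised to participate in either intervention or control group". On masking, the section says only that "the patients will be 'blinded' to which group they are in". No masking of GPs is claimed.
- **Training** (Intervention): control GPs: "The control group GPs will receive 2 hours of training in the primary care guideline for prevention of cardiovascular disease". The intervention workshops include "GP role plays relating to risk communication, shared decision-making principles, and primary prevention of cardiovascular disease in general practice", together with training in visual risk formats and a decision aid.
- **Order of events** (Intervention): "After participation in the workshop sessions, the GPs will return to their practices", and recruitment begins there.
- **Trigger for invitation** (Intervention): "When the GP identifies a patient with high cholesterol and is likely to suggest preventive pharmacological treatment, the GP will invite the patient".
- **Eligibility** (Participants): patients must "have high cholesterol corresponding to a recommendation for cholesterol-reducing medication according to Danish clinical guideline for general practice". Fixed exclusions follow.
- **Series** (Intervention): "Each GP will invite and recruit a minimum of 7 (consecutive) patients".
- **Outcomes** (Outcomes): the primary patient outcome is adherence to the treatment choice. GPs' attitudes to preventive cardiovascular treatment are a secondary GP outcome.

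**The concern.** In a cluster-randomised trial, randomisation balances practices. It balances patients only if they are found and invited in the same way in both arms. Here the person who invites has already had arm-specific training, and the last condition for invitation is that person's own inclination to suggest a drug. If training changes the inclination, it changes who enters the trial.

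Patients to whom a GP readily suggests medication may differ in risk, motivation and expected adherence from eligible patients over whom the GP hesitates. A difference in adherence between the arms could then partly reflect who was invited, or a real effect could be hidden. Intention-to-treat analysis does not help, because it protects only patients already recruited.

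**Working it through.** **1. Order of events.** The workshops differ by arm, so allocation precedes training, and the Intervention section places recruitment after training. The GPs themselves invite. The article describes no recruiter unaware of the arm and no list of eligible patients made before allocation.

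**2. Trigger against eligibility.** Participants asks for a guideline recommendation for medication. Intervention asks in addition that the GP be likely to suggest medication. A patient can meet the first and fail the second, so the second works as a further filter.

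**3. Can training move the filter?** Control GPs are taught the same guideline that defines eligibility. Intervention GPs are taught shared decision-making and risk communication. The protocol measures GP attitude to preventive treatment at baseline and at 6 months and lists it as an outcome. It therefore treats as a possible training effect the disposition on which the trigger depends.

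**4. What each safeguard covers.**

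| Safeguard | Covers | Leaves open |
|---|---|---|
| Guideline eligibility | Excludes patients outside the guideline | Which eligible patients are invited |
| Consecutive recruitment | Picking among triggered patients | Patients who never pass the trigger |
| Prevention content in both arms | Narrows the training contrast | The rest of the contrast |
| Stratification | Practice and GP features | Patients chosen later |
| Concealed allocation | Assignment of practices | The GP's knowledge of the training attended |

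**5. Scale.** The point rests on no sample-size figure, but the design assumptions show what size of shift would matter.

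Inputs from Sample size: 40 practices per arm and 7 patients each (40 × 7 = 280), non-adherence 20% against 10%, and 95% ranges across GPs of 0.08–0.50 and 0.04–0.25. The two-sided 5% level is from Data analysis.

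- Centres: √(0.08 × 0.50) = 0.20 and √(0.04 × 0.25) = 0.10.
- Log-scale SD: (ln 0.50 − ln 0.08)/(2 × 1.96) = 1.8326/3.92 = 0.4675. The other range gives the same value.

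*Stated power (90%).* Simulating each GP's rate as exp(N(ln p, 0.4675)) gives 87.4% (t-test on cluster means), 87.8–88.0% (cluster-robust Wald test on the log ratio) and 87.1–87.6% (random-intercept likelihood-ratio test). Other readings of the assumptions run from 83.6% (arithmetic means fixed at 20% and 10%) to 93.0% (logit-normal, centred at the interval midpoints on the logit scale). The stated 90% lies inside this range and is not shown to be wrong.

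*Assumed selection shift, no training effect.* Both arms keep the SD of 0.4675. One arm's typical non-adherence is 20%, and selection alone lowers the other's. These shifts are assumptions and are not in the documents.

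| Assumed shift (points) | Chance of p < 0.05 (t-test / Wald) |
|---|---|
| 0 | 4.9% / 5.1% |
| 2 | 8.1% / 8.5% |
| 3 | 12.8% / 13.2% |
| 5 | 29.1% / 30.0% |
| 8 | 66.4% / 67.2% |
| 10 | 87.1% / 87.7% |

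The shift is in the median GP rate. The mean rate is higher by a factor exp(0.4675²/2) = 1.115, so a 5-point shift moves the mean from about 22.3% to 16.7%.

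**The case against.** **The trigger may only describe timing.** Participants already requires a guideline recommendation and recruits when treatment options are to be discussed. A GP facing such a patient would usually be likely to suggest a drug, so the wording may not be meant as a second criterion. This is a fair reading, and it makes the fix easy to accept. It does not settle the point, because the sentence makes the GP's intention a condition of inviting.

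**Safeguards exist.** Recruitment is to be consecutive, and both arms receive some prevention training. Both facts stand and lower the risk. The consecutive rule follows the trigger sentence and is not defined against all eligible patients.

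**The analysis may adjust.** One might infer that the adherence analysis ignores patient baseline. The article does not support that. It names a multivariate binomial regression, and the covariate list is detail that an article commonly leaves to the analysis plan. Its absence is not part of this point.

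**The size is unknown.** This stands. A worked bias built on patients reluctant to take a drug would need invented shares and rates. It would also fit the mechanism poorly: the trigger concerns the GP's intention, and the Background allows that a chosen treatment may be no treatment, so a reluctant patient is not necessarily non-adherent.

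**The fix is partial.** This also stands. Trained GPs would still apply the criterion, and it comes from the guideline taught in the control arm. How objective that criterion is cannot be checked here, because the guideline is not at hand. Listing patients before allocation looks hard, since high cholesterol is usually found opportunistically.

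**Conclusion.** The point holds as a recruitment risk created by a stated rule. Trained GPs who know their training decide whom to invite, with a subjective condition added to guideline eligibility, and the protocol itself allows that training may change the attitude behind that condition. The existing safeguards reduce the risk without removing it.

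A reader might infer that the arms will differ, that the bias favours the intervention, or that it amounts to a given share of the 10-point target. The documents support none of these. They give no direction and no size, and selection could equally mask a benefit. The simulated percentages rest on assumed shifts and show only that a modest shift would matter. They are no estimate of what will happen. This is a cheap improvement to the recruitment rule and does not show the design to be invalid.

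**What to change.** 1. In Intervention, remove the GP's likelihood of suggesting medication as the trigger. Invite on the Participants criterion and exclusions alone, identically in both arms. This changes who is invited, not how anyone is treated.
2. Define consecutive as consecutive patients who meet that criterion.
3. Have each GP keep a short log of eligible patients not invited or declining, so that numbers and basic characteristics can be compared by arm.
4. As a supporting step, include prespecified patient baseline variables (such as age, sex and socio-demographic data) in the adherence model. Baseline cholesterol may be incomplete, because it is measured only on the GP's initiative. Adjustment cannot remove selection on unmeasured motivation.

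**Cost:** a wording change, a short log, and covariates already collected. Some invited patients will be ones to whom the GP would not have offered medication. Residual selection remains, because GPs who know their training still recruit; the log makes it visible but does not prevent it.

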### Development of the intervention

A preliminary draft for a training programme in risk communication and shared decision-making was developed by academic general practitioners and social scientists in the RISAP project group (PK, JT, MJ, AE, TL, BH, MR). The draft was based on literature review and experience from previous studies and entailed suggestions for improving ways to communicate about risk - including shared decision-making principles, visual representations of risk and risk reduction, decision support, and a patient decision aid.

61 GPs in Kolding, Region South, Denmark, were contacted by telephone by PK and BH, asking either the secretary or the GP permission to send a written invitation to a two-hour focus group interview. The invitations were sent directly to each of the GPs in the practices, with a note to return in an enclosed envelope to indicate willingness to participate (in Sept 2008). Participation was re-imbursed with a fee of 1400 DKK (165 £/188 €). 30 GPs returned the note, and 10 GPs (six male, four female) accepted participation on either of the two dates suggested in the written invitation, and two GPs (two female) offered participation on a later date. Average age was 48 years, ranging from 41 to 56 years.

The six GPs in the first focus group interview were first asked about their experiences with risk communication and decision-making with patients with high cholesterol. In the second half of the interview, the GPs were presented with the preliminary draft for the training programme. They were prompted to express their thoughts and ideas for further development from the preliminary draft. After the interview, these experiences, thoughts and ideas were categorised and interpreted, and members of the RISAP project group revised the preliminary draft accordingly. After the revision, the next two groups of GPs were interviewed, repeating the process of prompting and draft revision.

The GPs were asked to recruit at least one patient with high cholesterol deliberating cholesterol-reducing medication, for an individual interview with a researcher (PK). Four GPs recruited 12 patients, six male, six female. They were interviewed individually about their experiences with living with high cholesterol, treatment issues and with decision-making and risk communication with their GP. They were also presented with parts of the revised draft, i.e. the visual representations of risk and risk reduction, and the patient decision aid. They were prompted to express their thoughts and ideas for further development.

The data from the patient interviews were categorised and interpreted after the conclusion of the 12 interviews. The visual representations of risk and risk reduction and the draft decision aid were revised accordingly.

